##### Adherence

The German adherence scale OAS (OPTIE Adhärenzskala) is a clinician-rated measure to assess the willingness of the child and the caregiver to participate in the treatment and to follow the treatment recommendations [42]. It has been prepared for this project and is based on previous work [44]. In total, six items are rated on a four-point Likert-type scale (0 = *not at all* to 3 = *particularly*) and two scales are computed by the mean of the item scores (Child, Caregiver).

#### Progress report

The progress report contains the results of the online surveys and is provided to the therapist and the supervisor after each online survey. It consists of four sections (title page, notes, progress charts, appendix; see Fig. 2). The title page contains basic information about the case (e.g., patient’s name and birthdate) and a note section mainly made up of organizational information is intended to facilitate the handling of the progress feedback system and increase the treatment integrity (e.g., date of next supervision). The progress charts display the trajectories over the period of the questionnaire data at the scale level. And, finally, the appendix contains the results of the questionnaire data at the item level, but only for the latest online survey.

**Fig. 2 Fig2:**
[figure not shown]
Excerpt from the German OPTIE progress report. Note. The left panel contains the progress charts of the child rating regarding five outcome domains (symptoms, motivation, therapeutic alliance, treatment impact, goal attainment). The right panel is part of the appendix and shows the individual item answers for the last assessment grouped by scales. Individual items scores are colored to increase readability

#### Supervision

During the 12-month intervention period, therapists of the feedback condition receive five additional sessions of supervision lasting about 25 min each. These sessions are funded by the project. They are directed to support the application and the efficacy of the progress feedback system. The first session addresses the goal attainment scale ZIEBO and should take place 8 to 10 weeks after the start of therapy. The ZIEBO is part of the feedback system and therapists are requested to develop the personal goals with the patient and the caregivers at the beginning of the therapy. Under this supervision, the personal goals can be checked to ensure they are suitable for the therapy.

Supervision sessions two to five are intended to discuss the progress reports 3, 5, 7, and 9 from the online surveys 12, 24, 36, and 48 weeks after the start of the therapy, respectively, and to evaluate the treatment progress reports. During this supervision, it should be discussed if the treatment course is in line with the expectations of the therapist and the individual circumstances of a patient. In case of an unexpected or a negative trend, possible corrective measures should be discussed and the treatment planning should be adapted accordingly.

### Assessment

#### Schedule

For the group comparison (routine, feedback), data is collected at three assessments (pre, inter, post): at baseline before the beginning of the therapy as well as 6 and 12 months later (halfway through and at the end of the study-related intervention period).

#### Informants and blinding

For the assessments, five respondents are considered: (1) blinded clinician, (2) therapist, (3) caregiver, (4) child (≥ 11 years), and (5) teacher.

The blinded clinicians are study personnel and are responsible for the interviews with the caregivers. They are blinded for the treatment group (routine, feedback) and, whenever possible, also for the time of measurement (pre, inter, post), but this cannot be guaranteed. In general, interviews are conducted by telephone and are recorded whenever the caregivers give consent. There are two different means in the project of ensuring blinding for the treatment: one applies to interviewers who are involved in core processes of the study and who may have direct access to the project database, and the other applies to project staff with no direct access to the database and whose main responsibility is to conduct the interviews. To ensure blinding for the first group, the interview is organized by the project staff, and not by the person who is responsible for the interview. In this case, the interviewer is not aware of the identity of the telephone partner. For the second group, the interviewer may know the identity of the telephone partner (e.g., name), but will not know the treatment group. Either way, before the interview, the caregivers are requested not to reveal any sensitive information to the interviewer during the assessment (i.e., time of assessment, treatment group). In cases where the requirements for blinding of the treatment groups are not met, the audio record will be edited (when necessary) and will be rated again by a different blinded clinician. To ensure blinding for the time of the assessment, it is intended that a caregiver is interviewed by the same interviewer only once. However, for organizational reasons, the pre-assessment is difficult to blind and, in some instances, multiple ratings by the same interviewer for one family may occur.

The therapist is the practitioner responsible for the therapy. Caregivers refers to biological parents or guardians who support the child during therapy. The children, of 11 years and older, are the patients in the therapy. The study also includes younger children from the age of 6 years old. However, reports from those under the age of 11 are not considered for reasons of feasibility, reliability, and validity. The teacher may be the class teacher of the child or any other teacher with a more detailed knowledge of the behavior of the child. The teacher assessment will be conducted only if the caregiver and the child give their consent.

### Measures

As diagnostic measures, an interview and several questionnaires are used. The interview is rated by the blinded clinician. The questionnaires may be rated by different respondents depending on the particular instruments (i.e., blinded clinician, therapist, caregiver, child [≥ 11 years], teacher). All measures may be assessed up to three times (see Table 2). The primary outcome parameter is the total score of the clinical interview. Secondary outcome parameters may include all instruments measured at the post-assessment.

**Table 2 Tab2:** Measures of the pre-, inter-, and post-assessment at baseline and at 6 and 12 months after the beginning of the therapy

Measure	Domain	Assessment		
		Pre	Inter	Post
Blinded clinician				
SFSS-I	Symptoms – child	X	X	X
GBPF	Functioning – child	X	X	X
Therapist				
BADO	Basic documentation	X		X
GBPF	Functioning – child	X	X	X
FBB	Treatment satisfaction			X
Caregiver				
TOES	Outcome expectations	X		
CBCL/6–18 or BPM/6–18^a^	Symptoms – child	X	X	X
FBB-SCREEN	Symptoms and impairment – child	X	X	X
KIDSCREEN	Quality of life – child	X	X	X
FBB	Treatment satisfaction			X
Child (≥ 11 years)				
TOES	Outcome expectations	X		
YSR or BPM/6–18^a^	Symptoms – child	X	X	X
SBB-SCREEN	Symptoms and impairment – child	X	X	X
KIDSCREEN	Quality of life – child	X	X	X
FBB	Treatment satisfaction			X
Teacher				
TRF	Symptoms – child	X		X

*Note*. *SFFS-I* Symptoms and Functioning Severity Scale – Interview version (SFSS-I) [45], *GBPF* German rating scale for the assessment of the psychosocial functioning [46], *FBB* German questionnaire for treatment satisfaction [47], *BADO* German basic assessment system for psychotherapy [48], *TOES* Treatment Outcome Expectations Scale [40], *CBCL/6–18* Child Behavior Checklist for Ages 6–18 [43, 49], *BPM/6–18* Brief Problem Monitor for Ages 6–18 [37, 38], *FBB-SCREEN* German screening questionnaire for mental disorders and impairment [50]; *KIDSCREEN* Questionnaire for health-related quality of life [51], *YSR* Youth Self-Report, *SBB-SCREEN* German screening questionnaire for mental disorders and impairment [50], *TRF* Teacher Report Form [43, 49]

^a^BPM forms are short-forms of the CBCL/6–18 and YSR. The long-forms are used at pre- and post-assessment, the short-forms at the inter-assessment

#### Basic documentation

##### BADO

The German BADO (Basisdokumentation [Basic documentation]) [48] is a standardized measure for the assessment of essential data in psychotherapy and is rated by the therapist. The BADO admission form includes relevant information for the case preparation at the beginning of the therapy (e.g., social demographics, initial diagnosis, previous treatment) and the discharge form summarizes the treatment episode at the end of the treatment (e.g., final diagnosis, interventions during treatment) and includes recommendations for further treatment.

#### Treatment expectations

##### Treatment Outcome Expectations Scale (TOES)

The TOES (German translation: Therapieerwartungsskala [TES]) measures the anticipated treatment outcome and has forms for youths (TOES-Youth) and caregivers (TOES-Adult Caregiver) [40, 41]. Both forms contain eight items that are rated on a three-point Likert-type scale (1 = *I do not expect this* to 3 = *I do expect this*) and can be combined into a single score by the mean of the item scores (Total). Reported reliability coefficients (Cronbach’s α) are .91 for youths and .85 for adults [40]. The TOES may be used as a predictor for moderator analyses.

#### Symptoms – child

##### Symptoms and Functioning Severity Scale – Interview version (SFSS-I)

The SFSS-I is a newly developed 24-item semi-structured clinical interview in German [45]. All items stem from the Symptoms and Functioning Severity Scale (SFSS), which is part of the progress feedback system Peabody Treatment Progress Battery [40]. The SFSS is a global measure for symptom severity. It has been developed under consideration of the most common mental disorders in children and adolescents (i.e., attention-deficit/hyperactivity disorder, conduct disorder, oppositional defiant disorder, depression, and anxiety). In its original form, the SFSS is a questionnaire with forms for youths, caregivers, and clinicians that assess the progress feedback during treatment. The 24-item measure provides three scales (Internalizing, Externalizing, Total). All scales have shown good to excellent reliability (Cronbach’s α ≥ .88) [40].

There were four main reasons to develop the SFSS-I interview based on the items of the SFSS. First, the SFSS is a relatively brief measure that can be usefully applied under conditions of routine care. Second, the SFSS addresses broad domains of psychopathology (internalizing, externalizing). This is in line with the aim of the study and its sample: to analyze the efficacy of a progress feedback system in a general clinical sample of children and adolescents who exhibit either internalizing or externalizing problems but who have not been screened for a particular disorder. Third, the SFSS allows for a dimensional diagnostic approach (in contrast to a categorical approach) [52] and can be analyzed accordingly. Fourth, to the best of our knowledge, no other instrument satisfies the aforementioned conditions and can be applied to children aged 6 to 17 years old.

A manual was created during the development of the interview. It contains (1) the SFSS items themselves, (2) a newly developed detailed description of each item (i.e., meaning), and (3) a newly developed individual description of each item level. The additional item information is provided for the interviewer to clarify the content of the items and for exploration during the interview. The additional item level information is meant to increase the reliability of the item ratings. It was adapted from the German ILF (Interview-Leitfäden [Interview guidelines]) [53], a collection of semi-structured interviews for the assessment of disorders in children and adolescents. The rating scale of the SFFS-I was also adopted from the ILF, meaning that we used a four-point Likert-type scale (0 = *not presented*, 1 = *sometimes*, 2 = *often*, 3 = *very often*) instead of the original five-point scale of the SFSS (1 = *never*, 2 = *hardly ever*, 3 = *sometimes*, 4 = *often*, 5 = *very often*). This change was made given that the ILF interviews have shown good psychometric properties [54]. It is intended to adopt the scales of the SFSS for the SFSS-I (Total, Internalizing, Externalizing). The SFSS-I will be psychometrically evaluated before the scale scores are used [55]. The interview is rated by the blinded clinician and is conducted with the caregiver. It is the primary outcome parameter of the study.

##### ASEBA school-age Forms & Profiles (CBCL/6–18, YSR, TRF) and Brief Problem Monitor for Ages 6–18 (BPM/6–18)

The school-age forms measure the strengths and problems of children and youths [43, 49]. Versions for caregivers (Child Behavior Checklist for Ages 6–18 [CBCL/6–18]), youths (Youth Self-Report Form [YSR]), and teachers (Teacher’s Report Form [TRF]) are available and the study will mainly focus on three scales (Internalizing, Externalizing, Total Problems). Items are rated on a three-point Likert-type scale (0 = *not true* to 2 = *very true or often true*) and scale scores are computed by the sum of the item scores. For the scales under consideration in a German clinical sample, reliability coefficients (Cronbach’s α) were between .80 and .93 [49]. All three forms (CBCL/6–18, YSR, and TRF) will be used at pre- and post-assessment (see Table 1). At inter-assessment for parent and youth ratings, the BPM/6–18 short-forms for parents (BPM-P) and youths (BPM-Y) will be used instead (for instrument details see Section OPTIE Progress Feedback System) [37, 38].

##### FBB-SCREEN and SBB-SCREEN

The caregiver-rated FBB-SCREEN (Fremdbeurteilungsbogen zum Screening psychischer Störungen [Proxy-rating form for the screening of mental disorders]) and youth-rated SBB-SCREEN (Selbstbeurteilungsbogen zum Screening psychischer Störungen [Self-rating form for the screening of mental disorders]) are part of a German assessment system for mental disorders in children and adolescents [50] and are used to identify high-risk children and adolescents regarding mental health problems. Both forms contain 51 symptom items that are rated on a four-point Likert-type scale (0 = *not at all* to 3 = *very much*). Several symptom scales can be computed by the mean of the item scores (e.g., Conduct Disorder, Anxiety, Depression, Total). For most of the scales the reliability coefficients (Cronbach’s α) of both forms have been between .67 and .92 [50].

#### Functioning and impairment – child

##### GBPF

The German GBPF (Globale Beurteilung des psychosozialen Funktionsniveaus [Global assessment of psychosocial functioning]) is part of a German multi-axial classification scheme of mental disorders in children and adolescents based on ICD-10 [46]. The GBPF is a one-item clinical rating scale that measures functioning (e.g., psychological, social, school/occupational) due to a psychiatric disorder. Its item levels range from 0 (*excellent or good social adaptation in all areas*) to 8 (*needs constant care [24/7]*).

##### FBB-SCREEN and SBB-SCREEN

Both the caregiver-rated FBB-SCREEN and the youth-rated SBB-SCREEN contain five items to measure functional impairment and psychological strain [50]. The items are scored on a four-point Likert-type scale (0 = *not at all* to 3 = *very much*) and can be combined into a single scale by the mean of the item scores (Impairment).

#### Quality of life

##### KIDSCREEN-10 Index

The KIDSCREEN-10 Index measures health-related quality of life in children and adolescents [51] and provides forms for caregivers and youths. The items cover physical, psychological, and social aspects and are rated on a five-point Likert-type scale (1 = *not at all/never* to 5 = *extremely/always*). Both forms contain 10 items that each provide a single scale (Total). For the self-report form, a reliability coefficient (Cronbach’s α) of .82 has been reported [51].

#### Treatment satisfaction

##### FBB

The German FBB (Fragebogen zur Beurteilung der Behandlung [Questionnaire for the treatment assessment]) measures treatment satisfaction with a focus on the treatment process and the outcome quality of the therapy [47]. Forms for youths (FBB-P), caregivers (FBB-E), and therapists (FBB-T) contain 20, 21, and 26 items, respectively, and are rated on a five-point Likert-type scale (0 = *not at all/never* to 4 = *exactly/always*). A total scale as well as several subscales are provided. Scale scores are computed by the mean of the item scores. Depending on the form and the scale reported, reliability coefficients (Cronbach’s α) were between .71 and .94 [47].

## Methods and statistics

### Planned sample size and power calculations

For the sample size determination an effect size in the small to medium range was hypothesized. The calculation was done with Stata/SE (StataCorp LLC, College Station, TX, USA) under the presumption that the treatment groups (routine, feedback) would be compared using a two-sample *t*-test. The α-error was specified to be .05, the power to be .80, and the effect size (Cohen’s *d*) equal to .30. With these assumptions, the required sample size was 351 families. To compensate for attrition during the study (e.g., withdrawal of consent, treatment drop-out), the inclusion of 20% more patients than the required sample size was planned, resulting in a total sample size of 439 families.

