### Study therapists

The study therapists are post-graduate students trained at AKiP. In total there are around 150 therapists in training who provide psychotherapy under supervision as part of their practical education at the AKiP outpatient unit. All therapists in training hold a master’s degree or the German Diplom in various professions (e.g., psychology, pedagogy, social work, or rehabilitation science).

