### Randomization

Both patients and therapists are independently assigned to the two treatment conditions by stratified block randomization (block size: permuted block randomization of varying length; randomization ratio: 1:1). For patients, the stratification factors of gender (male, female) and the symptom domain (internalizing, externalizing, both) are considered. For therapists, the stratification is based on the factors of gender (male, female) and age (≤ 30, > 30). To maintain internal validity, therapists are randomized only once upon entry to the study and working with a second patient does not change their initial treatment group. Random assignment is done using the 24/7 Internet service ALEA (FormsVision BV, Abcoude, NL) which is maintained by the Institute of Medical Statistics and Computational Biology at the Faculty of Medicine and University Hospital Cologne, University of Cologne.

Two forms of randomization for patients are permitted: Regular randomization means that patients assigned to the routine group receive a therapist from the routine group and patients assigned to the feedback group receive a therapist from the feedback group. However, under conditions of routine care, the volume of patients is high and the initial study experience has shown that sometimes study therapists are unavailable. Thus, to ensure that patients can be enrolled and treated without delay, forced randomization is also permitted in exceptional cases [33]. This means that the patient is assigned post-hoc to an available study therapist from the other treatment condition and is also analyzed in this group (intention-to-treat).

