### Statistical analysis

The main purpose of the study is to evaluate the effectiveness of the progress feedback system and the primary analysis will concern the comparison of the feedback group and the routine group. Data will be analyzed by linear mixed-effects models [56]. All three assessments will be included (pre, inter, post) and the outcome at the pre-assessment will be used to adjust for baseline differences in the treatment groups [57]. Both the intention-to-treat as well as the per-protocol samples will be analyzed. However, the intention-to-treat analysis is considered the method of choice to preserve the integrity of the randomization process [58]. The secondary analyses will concern the participation behavior in the feedback group, the treatment drop-out, moderator and mediator analyses, and more.

Missing data will be analyzed, and recommended methods for adjustments will be applied (e.g., multiple imputation) [59]. Additionally, sensitivity analysis will be conducted to test the robustness of the assumptions when handling missing data.

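### The sample size calculation treats families as independent although they are nested in randomized therapists, so the stated 80% power needs a therapist design effect and the primary model should name a therapist effect

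*Protocol article*

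**What the plan says.** All references are to the protocol article.

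- *Planned sample size and power calculations*: the trial was sized "under the presumption that the treatment groups (routine, feedback) would be compared using a two-sample" *t*-test. With α at 5% and power at 80%, Cohen's *d* was set "equal to .30. With these assumptions, the required sample size was 351 families". The total of 439 adds an allowance for attrition and nothing else.
- *Randomization*: patients and therapists are both allocated ("randomization ratio: 1:1"), and "therapists are randomized only once upon entry to the study and working with a second patient does not change their initial treatment group". Under regular randomization a patient is treated by a therapist of the same arm. Under forced randomization the patient takes the arm of the therapist who is available.
- *Study therapists*: "In total there are around 150 therapists in training who provide psychotherapy under supervision".
- *Statistical analysis*: "Data will be analyzed by linear mixed-effects models". All three assessments enter, and the pre-assessment outcome is used for baseline adjustment. The section lists no random effects.

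**The concern.** Therapists are randomized units, each belongs to one arm, and each can contribute more than one family. Therapist is therefore nested in arm, not crossed with it. The intervention also acts through the therapist, who receives the progress reports and the extra supervision. Outcomes of families sharing a therapist are likely to be positively correlated, and between-therapist variance then enters the treatment contrast.

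There are two possible consequences, and they belong to alternative analyses:

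- If the analysis accounts for therapist, 351 families carry less information than 351 independent ones, and power at a true 5% level is below the stated 80% before any gain from covariates.
- If the analysis leaves therapist out, the treatment standard error is too small and the primary test rejects too often under the null.

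The article reports mostly small effects of progress feedback in earlier work. A result near the significance threshold is therefore plausible, and there the handling of therapist could decide the conclusion.

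**Working it through.** **Inputs from the article.** α = .05 (two-sided reproduces the figure; sidedness is not stated), power .80, d = .30, allocation 1:1, 351 analysed, 439 enrolled, around 150 therapists in the pool.

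**Assumptions, because the article gives no value.** Therapist ICC 0.02, 0.05, 0.10; coefficient of variation of caseload (CV) 0 or 0.6; number of participating therapists J = 150 (the whole pool) or 75 (half of it); pre–post correlation r = 0.3 or 0.5.

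**Step 1: reproduce the plan.** The exact noncentral *t* with 175 + 176 families gives power 0.8003; 350 families give 0.7991. So 351 is the smallest total that reaches 80% with independent observations. 351 / (1 − 0.20) = 438.75, rounded up to 439. Nothing in either figure allows for clustering.

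**Step 2: design effect.** DE = 1 + ((1 + CV²)·m − 1)·ICC, with m = 351/J. For J = 150, m = 2.34; for J = 75, m = 4.68.

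**Step 3: power of a cluster-corrected comparison at a true 5% level.** Effective N = 351/DE; power = Φ(0.30·√(effective N/4) − 1.96). With DE = 1 this gives Φ(2.81 − 1.96) = 80.2%, so the approximation is close to the exact value.

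**Step 4: type I error if therapist is left out.** 2·(1 − Φ(1.96/√DE)).

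**Step 5: gain from baseline adjustment.** Effective N is divided by (1 − r²), with the ICC assumed unchanged.

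Example, J = 150, CV = 0.6, ICC = 0.10: DE = 1 + (1.36 × 2.34 − 1) × 0.10 = 1.218; effective N = 351/1.218 = 288; power = Φ(2.546 − 1.960) = 72.1%; type I error without a therapist effect = 2·(1 − Φ(1.776)) = 7.6%.

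| J | CV | ICC | DE | Power, corrected, unadjusted | Type I error, therapist omitted | Power, corrected, r = 0.3 | Power, corrected, r = 0.5 |
|---|---|---|---|---|---|---|---|
| 150 | 0 | 0.02 | 1.027 | 79.2% | 5.3% | 82.8% | 89.3% |
| 150 | 0 | 0.05 | 1.067 | 77.7% | 5.8% | 81.4% | 88.1% |
| 150 | 0 | 0.10 | 1.134 | 75.1% | 6.6% | 79.0% | 86.2% |
| 150 | 0.6 | 0.10 | 1.218 | 72.1% | 7.6% | 76.1% | 83.6% |
| 75 | 0 | 0.02 | 1.074 | 77.4% | 5.9% | 81.1% | 87.9% |
| 75 | 0 | 0.05 | 1.184 | 73.3% | 7.2% | 77.3% | 84.7% |
| 75 | 0 | 0.10 | 1.368 | 67.1% | 9.4% | 71.2% | 79.2% |
| 75 | 0.6 | 0.10 | 1.536 | 62.1% | 11.4% | 66.2% | 74.5% |

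Referring the test to J − 2 degrees of freedom lowers corrected power slightly further: with equal caseloads and ICC 0.05, from 77.7% to 77.1% (J = 150) and from 73.3% to 72.2% (J = 75).

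**Step 6: the uncorrected *t*-test itself.** Its rejection rate at d = .30 is about Φ((2.81 − 1.96)/√DE): about 80%–78% with 150 therapists and 79%–75% with 75. It stays near 80% only because its true α is above 5%, as the type I error column shows.

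**The case against.** The strongest reply is that the *t*-test was only a sizing device. The planned analysis is a baseline-adjusted mixed model over three assessments, a class of model that can carry a therapist intercept. Listing random effects and degrees-of-freedom methods is what a journal article leaves to the full protocol or SAP, and neither is shown. At the only documented therapist number, 150, an assumed r = 0.5 gives 84%–89% power over the whole assumed range. ICC, caseload variation and J = 75 appear nowhere in the article.

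Most of this stands, and it limits the point. Four stronger readings are tempting, and the document does not support them:

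- *The primary analysis ignores therapist.* The article is silent on all random effects, so the type I error figures hold only if the full plan also omits therapist.
- *Power is lost and the type I error is inflated in the same analysis.* The first applies to a model with therapist, the second to one without.
- *The stated* t*-test has power as low as 62%.* That figure is for a cluster-corrected test; the uncorrected test rejects about 75% of the time in that scenario, at an inflated α.
- *150 is a ceiling on the number of therapists.* It is the size of the pool. Fewer may take part, and trainee turnover could raise the total.

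The reply does not remove the mismatch. The stated power rests on independence that the article's own randomization scheme contradicts. The gain from baseline adjustment is as undocumented as the ICC: at r = 0.3 and 150 therapists the range is 76%–83%, which straddles 80%.

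**Conclusion.** The point holds in a limited form. The 351 is arithmetically right for independent families. With more than one family per therapist on average, any positive therapist ICC puts the power of an unadjusted comparison at a true 5% level below the stated 80%. With 150 participating therapists the loss is modest: 79%–72% over ICC 0.02–0.10 and CV 0–0.6. With an assumed 75 it is larger: 77%–62%.

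The planned baseline adjustment may offset this (at r = 0.5, 84%–89% with 150 therapists and 74%–88% with 75), so it cannot be concluded that the trial is underpowered. Adjustment does not by itself protect the type I error. Without a therapist effect that error would be about 5.3%–7.6% (150) or 5.9%–11.4% (75), conditional on a model specification not shown.

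The nesting and the missing design effect are certain; the size rests on assumed ICC, caseload variation, number of participating therapists and pre–post correlation. Severity: should-fix.

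**What to change.** 1. In the primary mixed model, name a random intercept for therapist (nested in arm) alongside the patient-level structure, with Kenward-Roger or Satterthwaite degrees of freedom. If the full protocol or SAP already does this, a cross-reference is enough. Fix it before any unblinded analysis, so that the choice cannot depend on the result.
2. Restate the power for 351 analysed families as a range over therapist ICC and number of participating therapists, with the caseload assumption given and the expected gain from baseline adjustment shown separately.

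The 439 need not change, and neither does trial conduct. Therapists are allocated through the central randomization service, so which therapist belongs to which arm is already on record. The cost is one line of model specification and one recomputed power paragraph. The downside is slightly wider confidence intervals and a slightly less favourable stated power.
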